### Anticipated Challenges to Program Implementation

Our program, implemented in partnership with the district and state health department, is both a source of strength and a potential challenge. In the intervention arm, the program must navigate several systemic issues, including the double burden of noncommunicable and communicable diseases, reproductive health problems, underfunding, weak procurement and logistics systems (eg, supply of essential medicines and vaccines), an uneven distribution of HWs, weak regulatory mechanisms, and issues such as inappropriate prescription and use of medicines [31]. Through our handholding interventions and continuous engagement with stakeholders across the 3 tiers of the public health care system, we aim to mitigate some of these challenges.

Almost all the ANMs in UP have an internet-enabled smartphone or tablet. However, despite this universal access, a feasibility assessment and user feedback study conducted in Telangana with 2790 ANMs identified several digital challenges. These included permission restrictions for installing digital apps, poor internet speed, login difficulties, overheating or slow device performance, delays in receiving new content in digital apps, data inaccuracies, and issues with switching languages in the learning management system app. We expect similar digital challenges in the 2 intervention districts. The program addresses these issues through continuous handholding and support.

As our program does not work with private or unregulated health care sector, there is a lack of data on the capacity of these players in HRP management. However, in UP, around 30% of the ANC services were exclusively provided by private or NGO (nongovernmental organization) sector and an additional 13.5% by a combination of public or private or NGO sector providers [13,30]. This implies that our program interventions will not influence or will only partially influence 30%‐44% of pregnant women in the state. Also, women seeking ANC or HRP services from private or NGO providers are going to influence the quality of ANC indicators at community level.

### Rationale for the Study

#### Overview

The IHRPTM program in UP was developed with a comparative advantage, as it was informed by learnings from the implementation of 6 phase-1 protocols in Telangana and AP. In UP, the program was designed for a shorter duration (18 months vs 5 years in Telangana and AP), on a smaller scale (6 protocols vs 21 in Telangana and 20 in AP), and in a more limited geography (2 districts in UP vs 33 in Telangana and 26 in AP) as IHRPTM program was initiated as part of UP Government’s Ending Preventable Maternal Mortality (EPMM) initiative launched in mid-2024. As the impact evaluation of the IHRPTM program in Telangana and AP is going to take more time (2027 or beyond), the government of UP, before implementing the program at scale across all the 75 districts with around 20 HRP conditions, decided to first implement the program on a pilot basis. This pilot phase is of shorter duration (18 months), limited to 6 HRP conditions, and covers only 2 intervention districts. The 6 HRPs prioritized by the government of UP are quality ANC (QANC), anemia (moderate and severe), PIH, antepartum hemorrhage (APH; including placenta previa and abruptio placenta), heart disease or shortness of breath, and fever. Hence, the UP initiative was conceptualized as a pilot project, with the explicit aim of informing future scale-up across all 75 districts, expanding to additional HRP protocols, and generating early evidence of the program’s impact at both system and community levels.

While designing the impact evaluation of the UP pilot, the following contextual variations in the scale of direct beneficiaries were considered. The program engaged ANMs (>400 in UP vs >9000 in Telangana and >15,000 in AP), MOs (>100 in UP vs >1000 in Telangana and >1800 in AP), and specialists (>10 in UP vs >400 in Telangana and >500 in AP). Indirect beneficiaries also varied substantially, with approximately 60,000 pregnancies per year in UP compared with 700,000 in Telangana and 900,000 in AP, translating to roughly 18,000 HRPs per year in UP versus 200,000 in Telangana and 300,000 in AP. Training timelines also differed, while training all ANMs on 6 phase-1 protocols required approximately 1 year in Telangana and 9 months in AP, >400 ANMs in UP were trained in just a few days. Moreover, digital interventions were introduced within 2-3 months of program initiation in UP, compared with more than 3 years in Telangana and 1 year in AP, as these digital interventions were still evolving when implementation began in Telangana.

Thus, considering UP’s comparative advantage over Telangana and AP, sufficient number of direct and indirect beneficiaries, the rapid introduction of all interventions in quick succession, and additional scope for keeping a control arm, the UP impact evaluation design is expected to provide generalizable evidence on the program’s impact, even with its shorter duration (18 months) and smaller scale (2 intervention districts and 3 HRP protocols). In UP, the impact evaluation will be confined to the following 3 HRP conditions: anemia (moderate and severe), PIH, and APH.

#### Reasons for Not Conducting Impact Evaluation on the Below HRPs

Quality ANC is excluded from the impact evaluation as it is not an HRP condition but rather a set of well-established, evidence-based processes that health functionaries are expected to follow across the 3 levels of public health care system. ARMMAN has included QANC as one of the protocols as it sensitizes ANMs and MOs to the importance of a comprehensive history taking and conducting trimester-specific ANC examinations and tests, thereby contributing to overall quality of the ANC services. The program’s effect on QANC will be assessed using the following proxy indicators: proportion of women who received 3 essential tests and examinations (weight, hemoglobin, and blood pressure) in all the ANC visits, proportion of women who received a complete ANC package (at least 4 ANC visits, at least 1 tetanus toxoid injection, and consumed at least 100 IFA tablets or consumed IFA for a minimum of 100 days), and proportion of women whose third trimester ANC visit took place at CHC or higher-level facility.

Heart disease or shortness of breath is excluded from impact evaluation due to its low prevalence (0.3%‐3.5%) [32]. Evaluating changes for a condition with such a low prevalence over an intervention period of 18 months would require an unfeasibly large sample size of recently delivered women (RDW) with the condition. Also, severe cases with this condition require care at medical college hospitals or specialized facilities with 24×7 availability of cardiologists, surgeons, anesthetists, etc [33], are beyond the scope of this program.

Fever in pregnancy is excluded from impact evaluation, as it is generally a comorbidity associated with non-HRP conditions (eg, dengue, hepatitis E, urinary tract infection, and vector- or water-borne diseases) [34].

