#### Hypothesis and Outcomes

The program’s impact evaluation will test the following research hypotheses: (1) Does the program, implemented over 18 months, enhance knowledge, skills, and confidence of the ANMs and the MOs to make early diagnosis and manage the 3 HRPs in the intervention arm, compared to usual care arm? (2) Can the capacitated ANMs and MOs translate their knowledge and skills into practice, particularly for early diagnosis and end-to-end management of the 3 HRP conditions in the intervention arm, compared to the control arm? (3) Does the program improve the quality of ANC services in the intervention arm, compared to the usual care arm?

At the system level, the primary outcomes focus on changes in the knowledge and skills of HWs. The first outcome is the net change in correct knowledge and skills of ANMs to manage (treat, counsel, refer, and follow-up) women with any of the 3 HRP conditions (anemia, PIH, and APH) from baseline to end line, comparing intervention and control arms. The second outcome is the net change in correct knowledge and skills of MOs to manage (treat, counsel, refer, and follow-up) women with any of the 3 HRP conditions (anemia, PIH, and APH) from baseline to end line, comparing intervention and control arms. The percentage of correct knowledge and skills for ANMs and MOs will be calculated based on the number of correct responses provided out of a total of 45 questions on the 3 HRPs, administered at baseline and end line surveys.

The system-level secondary outcomes include the net change in the ability of ANMs to correctly identify HRP-related signs and symptoms from baseline to end line, in intervention versus control arm and net change in the ability of MOs to do the same. Other outcomes include changes in the confidence level of ANMs and MOs to manage HRPs between baseline and end line across 2 arms and to document qualitatively whether any systematic barriers reported by district officials at baseline survey were overcome by the end line, by comparing intervention and control arms.

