At the community level, the primary outcome includes net change in the proportion of RDW with any of the 3 HRP conditions (anemia, PIH, and APH) whose problem was resolved prior to delivery and who reported satisfaction with the management of the condition, from baseline to end line, in intervention versus control arm. Satisfaction level of RDW is measured using a 5-point Likert scale on the topics of “attitude and behavior of staff,” “cleanliness and hygiene,” “comfort and care,” and “overall satisfaction with management of HRP condition at the facility.”

The community-level secondary outcomes include net change in proportion of RDW who received the complete ANC package during their last pregnancy*,* from baseline to end line, in intervention versus control arm. Also includes the net change in proportion of RDW who were sensitized about HRPs by ANM or MO during their last pregnancy*,* during baseline and end line, in intervention versus control arm. Other secondary outcomes include net change in the mean gestational month of first diagnosis of 3 HRPs by an ANM*,* from baseline to end line, in intervention versus control arm, and net change in the proportion of RDW diagnosed with any of the 3 HRPs who received protocol-based management or referral from an ANM*,* from baseline to end line, in intervention versus control arm. We also measure the net change in proportion of RDW diagnosed with any of the 3 HRPs, received protocol-based management or referral from MO*,* from baseline to end line in intervention versus control arm.

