### Study Geography

For this study, the government of UP has identified Shravasti and Sambhal as the intervention districts to implement the program. Keeping in view the 2-arm nature of the study, the study team has identified 2 usual care arm districts that closely match with the intervention districts using latest socio-demographic, antenatal, and immediate postpartum care indicators for the district (NFHS-5, 2019‐2021) [13]. Identified Gonda as the matching usual care arm district for Shravasti. The distance between these 2 districts is less than 50 km. Identified Budaun as matching usual care arm district to Sambhal. The distance between these 2 districts is less than 100 km. Table 1 provides sociodemographic and ANC and delivery practices in 4 study districts, and Figure 2 depicts the 4 study districts. The matched control districts were approved by the government of UP.

**Table 1. T1:** Sociodemographic and health care–seeking profile of 4 study districts.

	Intervention arm districts		Usual care arm districts	
	Shravasti	Sambhal	Gonda	Budaun
Sociodemographic profile^a^				
Population (2011), n	1,117,361	2,199,774	3,433,919	3,681,896
Sex ratio of population, (females per 1000 males)	881	891	921	871
Urban population, %^b^	4	3	7	22
Tahsils, n	3	3	4	6
Villages, n	541	993	1817	2061
Literacy, %^b^	47	55	59	53
Scheduled caste population, %^b^	16.9	16.6	15.5	17.7
ANC^c^, delivery, and immediate postpartum care indicators (2019‐2021)^d^, %^e^				
Received at least 4 ANC visits	42.3	32.9	41.7	40.6
Mothers protected against tetanus toxoid	94.4	90.3	90.4	90.1
Mothers who consumed 100 iron-folic acid	16.6	21.3	17.2	15.9
Institutional births	80.4	74.2	81.8	72.3
Mothers who received postnatal care in 2 days	68.3	67.5	68.6	62.4
Mothers received MCP^f^ card	95.9	93.5	97.1	94.4

a Master data: Census 2011-state and district wise primary census abstract.

b These are census percentages.

c ANC: antenatal care.

d International Institute for Population Sciences (IIPS) and ICF. 2021. National Family Health Survey-5, India, 2019‐21: Uttar Pradesh. Mumbai: IIPS.

e Weighted percentages.

f MCP: Mother and Child Protection.

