### Triangulation of Mixed Methods Data

As part of the impact evaluation, one of the hypotheses being tested is “‘whether capacitated ANMs and MOs are able to translate their knowledge and skills to manage HRPs into practice.” This hypothesis will mainly be tested by triangulating both the datasets on the listed themes and indicators, particularly, during the end line (Table 5).

**Table 5. T5:** How qualitative and quantitative datasets will be triangulated and integrated?

Theme or indicator	System level data (qualitative)	Community level data (quantitative)
Training and handholding of ANMs^a^ and MOs^b^ on HRPs^c^	Early diagnosis of HRPs reported by ANMs or MOs Improved knowledge and skills to manage HRPs by ANMs and MOs Improved confidence to manage HRPs	Proportion of HRPs diagnosed in the first trimester Protocol-based management of HRPs Protocol-based referral of HRPs Proportion of unnecessary or irrational referrals
Motivation and satisfaction of ANMs and MOs	Digital tools facilitating improved counseling and follow-up of women with HRPs by ANMs and MOs	Proportion of mothers with HRPs counseled and followed up by ANMs and MOs Proportion of mothers with HRPs highly satisfied with management and referral practices of ANMs and MOs
Quality ANC^d^	Improvement in quality of ANC services reported by ANMs and MOs	Proportion of mothers whose weight, hemoglobin, and blood pressure were collected at least 4 times in pregnancy Proportion of mothers who received complete ANC package of services
Facilitators and barriers to HRP management	Specific nuances of facilitators and barriers to HRP management reported by system stakeholders	Proportion of mothers with HRPs using public health facilities for management Proportion of mothers using public health facilities for ANC, delivery, and PNC^e^ care

a ANM: auxiliary nurse midwife.

b MO: medical officer.

c HRP: high-risk pregnancy.

d ANC: antenatal care.

e PNC: postnatal care.

To operationalize triangulation as a methodological practice, the study will use structured integration matrices, defined timelines, and clearly delineated roles. The process will take place during the end line analysis phase (March-June 2026), once both qualitative and quantitative datasets have been collected and validated.

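### The three-test quality-ANC proxy is defined in two incompatible ways, and the all-visits version can only stay level or fall as women make more visits at unchanged per-visit care

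*Protocol article*

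**What the plan says.** The section on reasons for not conducting impact evaluation on certain conditions explains that quality ANC is not itself a high-risk condition. It then says "The program’s effect on QANC will be assessed using the following proxy indicators". The first of the three proxies is the "proportion of women who received 3 essential tests and examinations (weight, hemoglobin, and blood pressure) in all the ANC visits". The second is the "complete ANC package (at least 4 ANC visits, at least 1 tetanus toxoid injection", plus an iron-folic acid requirement.

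Table 5, in the section on triangulation of mixed methods data, has a row for quality ANC. Its quantitative column also pairs a three-test indicator with the complete ANC package, but the three-test indicator is now the "Proportion of mothers whose weight, hemoglobin, and blood pressure were collected at least 4 times in pregnancy".

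The third research hypothesis asks: "Does the program improve the quality of ANC services in the intervention arm, compared to the usual care arm". Under Hypothesis and Outcomes, "The community-level secondary outcomes include net change in proportion of RDW who received the complete ANC package during their last pregnancy". Neither version of the three-test indicator is listed there as an outcome.

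**The concern.** Both places use the same three measurements, under the same construct and next to the same companion indicator, but the pass rules differ. One rule asks whether every visit made was complete. The other asks whether enough measurements accumulated over the pregnancy.

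The all-visits rule sets no floor on the number of visits. If care at each visit does not change, an added visit gives a woman one more chance to fail and none to recover. Yet more visits are an intended effect, because four visits are part of the complete ANC package, which is both the companion proxy and a listed secondary outcome. The Data Analysis section treats the net change in each output or outcome indicator as the causal effect of the intervention. Differencing does not remove a shift in visits that the programme itself causes. Adjusting for the visit count would not be a clean remedy either, because that count is measured after the intervention begins.

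At stake is the sign of one of three quality-ANC proxies. There is also room to choose between two definitions after results are seen, although Study Design promises a locked analysis plan.

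**Working it through.** The protocol gives no figure for this indicator, so there is nothing to reproduce.

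**Step 1. The two rules side by side** (counting a visit as complete when all three measurements are taken):

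| Visits made | Complete visits | All-visits rule | At-least-4 rule |
|---|---|---|---|
| 1 | 1 | pass | fail |
| 3 | 3 | pass | fail |
| 4 | 4 | pass | pass |
| 5 | 4 | fail | pass |

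The rules disagree in both directions. For a given woman, an extra visit can only keep the all-visits result or turn it from pass to fail. It can only keep the at-least-4 result or turn it from fail to pass. This holds whatever the dependence between visits.

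**Step 2. Inputs.** From Table 1, row "Received at least 4 ANC visits": Shravasti 42.3%, Sambhal 32.9%, Gonda 41.7%, Budaun 40.6%. Most women are below four visits, so there is room to rise. The following are assumed, because the protocol does not give them:
- the share with at least 4 visits goes from 40% to 55% in the intervention arm and does not change in the control arm;
- women below four make 2 visits and the others make 5;
- per-visit completeness is p = 0.8;
- the within-woman correlation ρ ranges from 0 to 1.

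**Step 3. Independent visits (ρ = 0), p fixed at 0.8.**

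All-visits rule, P = p^k: 0.8² = 0.640 and 0.8⁵ = 0.328.
- Before: 0.40 × 0.328 + 0.60 × 0.640 = 0.515
- After: 0.55 × 0.328 + 0.45 × 0.640 = 0.468
- Change: **-4.7 points**

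At-least-4 rule: 0 with 2 visits; with 5 visits, 5 × 0.8⁴ × 0.2 + 0.8⁵ = 0.737.
- Before: 0.40 × 0.737 = 0.295
- After: 0.55 × 0.737 = 0.406
- Change: **+11.1 points**

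**Step 4. Correlated visits and better testing.** For 0 < ρ < 1 the number of complete visits is taken as beta-binomial with mean p. At ρ = 1 a woman's visits are all complete or all incomplete. Changes are in percentage points.

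| ρ | All-visits, p stays 0.80 | At-least-4, p stays 0.80 | All-visits, p rises to 0.85 | p at which all-visits is level |
|---|---|---|---|---|
| 0 | -4.7 | +11.1 | +5.4 | 0.824 |
| 0.3 | -2.5 | +10.9 | +6.1 | 0.815 |
| 0.6 | -1.2 | +11.3 | +5.9 | 0.809 |
| 1 | 0.0 | +12.0 | +5.0 | 0.80 |

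Check of the break-even at ρ = 0: 0.55 × 0.824⁵ + 0.45 × 0.824² = 0.55 × 0.380 + 0.45 × 0.679 = 0.515, the starting value.

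**The case against.** A reader might infer that a programme that increases ANC would necessarily look as if it had worsened quality. The document does not support that. The quality-ANC protocol directly targets "conducting trimester-specific ANC examinations and tests, thereby contributing to overall quality of the ANC services", so per-visit completeness is meant to rise too, and a small gain offsets the fall. The programme does not work directly with pregnant women, so a rise in visits is the less direct effect. Only a rise beyond that in the control arm enters the difference-in-difference estimate; a common rise largely cancels.

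A reader might also take a woman-level contrast as the size of the bias. Going from 3 to 5 visits lowers the pass probability from 0.9³ = 72.9% to 0.9⁵ = 59.0%, or from 0.8³ = 51.2% to 0.8⁵ = 32.8%. Those falls of 14 and 18 points assume independence, and would apply to an arm only if every woman moved from 3 to 5 visits.

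Nor is the third hypothesis left without a sound measure. The complete ANC package is the listed ANC outcome, it has a visit floor, and this defect does not touch it.

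It can fairly be said that the protocol never states that the two versions are one indicator, and that content and coverage may legitimately be measured separately. But the parallel pairing makes a single indicator the natural reading, and the text does not present them as two measures. The Table 5 rule also has a cost. Barring measurements outside ANC visits, it fails every woman below four visits, about 58% to 67% on the Table 1 figures, however good her care. Denominators and women with no visit can be left to an analysis plan; two conflicting stated definitions cannot be excused that way.

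**Conclusion.** The point holds as a conflict of definition plus a structural weakness in one of the two versions. The conflict and the direction of the weakness rest on no assumption. The size does: under the assumed shift with completeness fixed at 0.8, the all-visits version changes by between -4.7 and 0 points depending on within-woman correlation, while the at-least-4 version rises by about 11 to 12. The two can therefore give opposite signs on the same data, and the all-visits version could mask or reverse a real gain. Whether it does depends on visits rising more than under usual care without a modest gain in per-visit testing. The consequence is confined to a proxy outside the listed primary and secondary outcomes.

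**What to change.** Before the end line analysis (March-June 2026), put one definition in both places and state its denominator, including women with fewer than four visits or none. One option is all three measurements taken at least 4 times, among all recently delivered women. Next to it, report per-visit completeness (fully tested visits divided by total visits) and the number of visits, by arm and survey, so that content and coverage are read separately.

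This needs no new data collection: Table 3 lists a photograph of the Mother and Child Protection card with details of each ANC visit. Where those details exist only as a picture, they must be abstracted, which any version of the indicator would require. The small downside is that the at-least-4 version partly overlaps with the four-visit component of the complete ANC package, which is why per-visit completeness should be shown with it.

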#### Hypothesis and Outcomes

The program’s impact evaluation will test the following research hypotheses: (1) Does the program, implemented over 18 months, enhance knowledge, skills, and confidence of the ANMs and the MOs to make early diagnosis and manage the 3 HRPs in the intervention arm, compared to usual care arm? (2) Can the capacitated ANMs and MOs translate their knowledge and skills into practice, particularly for early diagnosis and end-to-end management of the 3 HRP conditions in the intervention arm, compared to the control arm? (3) Does the program improve the quality of ANC services in the intervention arm, compared to the usual care arm?

At the system level, the primary outcomes focus on changes in the knowledge and skills of HWs. The first outcome is the net change in correct knowledge and skills of ANMs to manage (treat, counsel, refer, and follow-up) women with any of the 3 HRP conditions (anemia, PIH, and APH) from baseline to end line, comparing intervention and control arms. The second outcome is the net change in correct knowledge and skills of MOs to manage (treat, counsel, refer, and follow-up) women with any of the 3 HRP conditions (anemia, PIH, and APH) from baseline to end line, comparing intervention and control arms. The percentage of correct knowledge and skills for ANMs and MOs will be calculated based on the number of correct responses provided out of a total of 45 questions on the 3 HRPs, administered at baseline and end line surveys.

The system-level secondary outcomes include the net change in the ability of ANMs to correctly identify HRP-related signs and symptoms from baseline to end line, in intervention versus control arm and net change in the ability of MOs to do the same. Other outcomes include changes in the confidence level of ANMs and MOs to manage HRPs between baseline and end line across 2 arms and to document qualitatively whether any systematic barriers reported by district officials at baseline survey were overcome by the end line, by comparing intervention and control arms.

At the community level, the primary outcome includes net change in the proportion of RDW with any of the 3 HRP conditions (anemia, PIH, and APH) whose problem was resolved prior to delivery and who reported satisfaction with the management of the condition, from baseline to end line, in intervention versus control arm. Satisfaction level of RDW is measured using a 5-point Likert scale on the topics of “attitude and behavior of staff,” “cleanliness and hygiene,” “comfort and care,” and “overall satisfaction with management of HRP condition at the facility.”

The community-level secondary outcomes include net change in proportion of RDW who received the complete ANC package during their last pregnancy*,* from baseline to end line, in intervention versus control arm. Also includes the net change in proportion of RDW who were sensitized about HRPs by ANM or MO during their last pregnancy*,* during baseline and end line, in intervention versus control arm. Other secondary outcomes include net change in the mean gestational month of first diagnosis of 3 HRPs by an ANM*,* from baseline to end line, in intervention versus control arm, and net change in the proportion of RDW diagnosed with any of the 3 HRPs who received protocol-based management or referral from an ANM*,* from baseline to end line, in intervention versus control arm. We also measure the net change in proportion of RDW diagnosed with any of the 3 HRPs, received protocol-based management or referral from MO*,* from baseline to end line in intervention versus control arm.

